#### Poolability and Other Analyses

Univariable Cox regression analyses of the primary efficacy end points and all other time-to-event end points (ie, overall survival, time to symptomatic progression, and time to deterioration in quality of life) will be conducted with the following baseline factors, one at a time, together with randomized group: age group, race, ethnicity, gender, unilobar versus bilobar disease, oxaliplatin or irinotecan first-line chemotherapy, KRAS status, ECOG performance status, region, duration of time from date of diagnosis of mCRC to randomization, duration of time from the start of first-line chemotherapy to date of progression on first-line therapy, duration of time from date of progression on first-line therapy to date of start of second-line chemotherapy, synchronous versus metachronous metastases, location of primary tumor at the time of first diagnosis of primary colorectal cancer (right-sided vs left-sided), tumor burden, and presence of lung or lymph node lesions. Receipt of oxaliplatin- or irinotecan-based second-line chemotherapy and the receipt of biological agents during the study will also be assessed one at a time. This will allow an assessment of each of these factors on the study outcomes.

To assess the poolability of data across study sites, multivariable Cox regression analyses of the time-to-event end points will be conducted, including factors of randomized group, study site, randomized group by study site interaction, and the factors from the univariable analyses that have a one-sided *P*<.075. Similarly, to assess the poolability of data across regions, Cox regression analysis will be conducted with study site replaced by region.

Logistic regression analyses of the binary end points (ie, objective response rate and disease control rate) will be conducted in the same way as the Cox regression analyses described above.

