### Chemotherapy

The treatment schema is shown in Figure 1.

For both groups, second-line chemotherapy started within 21 days of randomization. If during the first-line chemotherapy, patients had received an oxaliplatin-based regimen, then during the EPOCH study, they receive a standard-of-care irinotecan-based chemotherapy. Those who received an irinotecan-based regimen as first-line therapy receive a standard-of-care oxaliplatin-based regimen in this study. Generally, second-line chemotherapy is given every 2 weeks for 6 to 12 cycles; chemotherapy is continued at the investigator’s discretion.

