**Figure 1 figure1:**
[figure not shown]
Clinical trial schema for the TheraSphere microspheres EPOCH study. Eligible patients have a washout period of at least 14 days from previous chemotherapy and biologic agents. Second-line chemotherapy is started within 21 days of randomization. Control group: biologic agents are permitted starting at the first cycle of second-line chemotherapy. TARE group: biological agents are discontinued at least 28 days before TARE and are not permitted until the first cycle of second-line chemotherapy that occurs after TARE. HPFS: hepatic progression-free survival; PFS: progression-free survival; TARE: transarterial radioembolization with TheraSpheres™ microspheres.

Control group patients can receive biological agents starting with the first cycle of second-line chemotherapy. For the TARE group, one cycle of chemotherapy is administered before the TheraSphere treatment, and biological agents may only be added to the first cycle of chemotherapy regimen that occurs after the TheraSphere administration.

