### Transarterial Radioembolization

In the TARE group, TheraSphere microspheres are administered in place of the second cycle of chemotherapy. The treatment approach for TheraSphere can be lobar or selective. Patients with unilobar disease receive TARE to the diseased lobe. Patients with bilobar disease receive treatment to both lobes via successive lobar infusions during the same treatment session. Biological agents must be discontinued for at least 28 days before TARE. Chemotherapy resumes 2 weeks after TARE, at which time treatment with biologic agents may be started.

Eligibility for TARE with TheraSphere microspheres is determined by evaluations that include a pretreatment angiography with technetium-99m macroaggregated albumin (^99m^Tc-MAA), followed by a^99m^Tc-MAA single-photon emission computed tomography (SPECT) or SPECT-CT scan to assess the potential for shunting microspheres to the lungs as well as the potential for the deposition of microspheres to the gastrointestinal tract. Repeat^99m^Tc-MAA may be needed for subsequent treatments to estimate cumulative lung shunt or to reassess gastrointestinal shunting. Patients are ineligible for TARE if radiation exposure to the lungs exceeds 30 Gy (or 50 Gy cumulative across all planned infusions, estimated during the dose calculation) or embolization cannot be performed to effectively block gastrointestinal blood flow from the hepatic arterial system. Randomized patients deemed ineligible for TARE continue with the planned second-line chemotherapy.

Radioembolization can be performed via a segmental or lobar approach, depending on operator preference and angiographic anatomy. The targeted administered dose is 120±10% Gy to the target volume, based on a single-compartment Medical Internal Radiation Dose model [23].

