### Treatment for Disease Progression

After disease progression is observed and confirmed, patients in either group may receive the best alternative therapy or care that the investigator considers appropriate. Patients in the TARE group who have hepatic progression with hepatic lesions that are still amenable to TheraSphere are eligible for repeat treatment with TheraSphere. In these patients, TheraSphere may be administered at the investigator’s discretion on separate treatment days. Although this is not a cross-over study, patients in the control group who have hepatic progression with hepatic lesions that are amenable to liver-directed therapy can receive TheraSphere or any other liver-directed therapies according to the investigator’s decision. As with the initial administration of TheraSphere, biological agents must be discontinued for at least 28 days before any additional TheraSphere administration.

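### Receipt of biological agents, a post-randomization factor with no limit on line or timing, is screened and modelled with the baseline factors; read as ever-received it is biased, in a direction that depends on what is counted (minor)

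*Protocol article*

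**What the plan says.** Under Poolability and Other Analyses, the protocol article lists baseline factors for Cox models fitted one factor at a time with randomized group. It then adds second-line regimen and states that "the receipt of biological agents during the study will also be assessed one at a time". The multivariable models for poolability across sites and regions take "the factors from the univariable analyses that have a one-sided" P<.075, with no exemption for factors that arise after randomization. For objective response and disease control, logistic models "will be conducted in the same way as the Cox regression analyses described above". The Discussion names biological agents received among the important covariates.

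The permitted start differs by group. Under Chemotherapy, for both groups "second-line chemotherapy started within 21 days of randomization". The text with Figure 1 says "Control group patients can receive biological agents starting with the first cycle of second-line chemotherapy", whereas in the TARE group "biological agents may only be added to the first cycle of chemotherapy regimen that occurs after the TheraSphere administration". Transarterial Radioembolization adds: "Chemotherapy resumes 2 weeks after TARE, at which time treatment with biologic agents may be started". After progression, "patients in either group may receive the best alternative therapy or care that the investigator considers appropriate" (Treatment for Disease Progression), and Table 1 has later chemotherapy and concurrent medication recorded up to death or end of study. Screening and Eligibility says the intended regimen, with any biologic, is decided before randomization.

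**The concern.** A patient must live long enough to receive a biologic. If receipt is coded ever/never, anyone who dies before the permitted date counts as a non-receiver, and the receivers are credited with survival the drug did not cause. The wait is about four weeks longer in the TARE group.

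The open wording adds a second problem. Agents given in later lines also count as receipt during the study. For progression-free survival those agents follow the event, so they move patients who have already progressed into the receiver group and push the HR up. For overall survival a later-line agent requires survival to progression and beyond, which pushes the HR down.

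At stake is the answer to a question the article says it wants answered, namely how this factor relates to the outcomes, and whether the factor enters the multivariable models for a reason unrelated to any biologic effect.

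**Working it through.** The article gives no figure for this analysis apart from the .075 threshold, so there is none to reproduce.

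**Timing, from the article.** First chemotherapy falls on day 0-21. TARE replaces the second two-weekly cycle (+14 days) and chemotherapy resumes 14 days after that. A biologic is therefore first possible on day 0-21 in control and day 28-49 in TARE, with midpoints 10.5 and 38.5. The first scheduled scan is at 56±7 days (day 49-63), and scans within six weeks of randomization are not counted. On schedule, no counted scan precedes the biologic date, so early death is what creates immortal time.

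**Assumptions, not in the article.** No true biologic effect; intended use u = 50-80%; deaths by day 56 d = 1-3% at constant hazard; disease control p = 70-90% among patients alive at the first scan; 20-40% of progressors given a later-line biologic.

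**Deaths before the biologic date.** With hazard h = -ln(1-d)/56, q = 1 - exp(-h × midpoint).
- d = 1%: h = 0.000179; q = 0.19% control, 0.69% TARE.
- d = 3%: h = 0.000544; q = 0.57% control, 2.07% TARE.

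**Disease control (ever/never coding).** A patient dead by day 56 is not controlled. Let s = (1-d)p. Within a group, receivers are a fraction u(1-q), of whom us are controlled. Non-receivers are (1-u) + uq, of whom (1-u)s are controlled. Hence

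OR = [1 - s + q·u/(1-u)] / [1 - s - q].

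Example with d = 3%, p = 80%, u = 80%: s = 0.776 and 1 - s = 0.224.
- Control: (0.224 + 4 × 0.0057) / (0.224 - 0.0057) = 0.2468/0.2183 = 1.13.
- TARE: (0.224 + 4 × 0.0207) / (0.224 - 0.0207) = 0.3068/0.2033 = 1.51.
- Geometric mean as an approximate arm-adjusted value: √(1.13 × 1.51) = 1.31. A simulated logistic fit gave 1.33.

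The extremes by the same formula:

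| d | p | u | Control | TARE | Combined |
|---|---|---|---|---|---|
| 1% | 70% | 50% | 1.01 | 1.05 | 1.03 |
| 1% | 90% | 80% | 1.09 | 1.34 | 1.21 |
| 3% | 70% | 50% | 1.04 | 1.14 | 1.09 |
| 3% | 90% | 80% | 1.24 | 1.97 | 1.56 |

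For objective response, assumed at 20%, the simulated OR is only 1.01-1.08.

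**Cox models (simulation).** Inputs were a control median of 6 months, HR 0.71 for TARE, 8-weekly scans, and Cox models with group plus receipt.

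| Ever-received term | HR with no true effect |
|---|---|
| PFS, second-line receipt only | about 0.91-1.00 |
| PFS, later lines counted | about 0.96-1.14 (above 1 in 6 of 8 settings) |
| OS, later lines counted | about 0.82-0.98 |

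A second simulation with simpler censoring gave 0.93-0.99 for the first row and 0.97-1.22 (above 1 in 7 of 8) for the second. Hepatic progression-free survival was not simulated.

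**Selection at one-sided P<.075 (PFS, second-line receipt only).** The ever-received term is selected in 10-22% of trials and a time-dependent term in 8-10%.

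**Effect on the treatment comparison.** Replacing received by intended use moves the TARE HR by at most 0.0003 for PFS and 0.003 for OS, and the group-by-region HR ratio by 0.0001. The site interaction was not simulated.

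**The case against.** The best defence is that the article never says ever-received. Receipt appears in a separate sentence after the baseline list closes, and an article may leave the coding of a covariate, the line that counts and the window to the analysis plan. This stands for the Cox models: ever/never is the natural reading beside fixed factors, but it is a reading. It does not stand for the logistic models, where time-dependent coding is unavailable. Nor does it remove what the text does state, which is a post-randomization factor, an open period, the shared P<.075 screen and the extension to binary end points.

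A second defence is that the imaging rules already limit immortal time for the progression end points. This also stands. With on-schedule starts and no event before six weeks, simulation gives an HR of 1.01 and selection in 5% of trials. What remains for second-line receipt comes from early death and is small.

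Two stronger readings are tempting. A reader might infer that the factor always flatters biologics. The documents do not support that, because the wording that admits later lines usually turns the PFS bias towards harm. A reader might also infer large distortions: HRs of 0.83, 0.73 and 0.47 can be simulated. The first needs progression events from day 0, contrary to the scan rules. The other two spread starts over 6 and 12 months, whereas the article ties the permitted start to cycle 1 or to the first cycle after TARE.

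**Conclusion.** The point holds as a minor one. As worded, the factor can show a biologic effect where there is none: in either direction for progression-free survival, and towards benefit for overall survival and disease control. The disease control bias is the firmest result because its coding is forced. It also differs by group, so the schedule alone could suggest that biologics work better with TARE. All sizes rest on assumed use, early-death, disease control and later-line rates, and the largest sit at 3% early deaths with 80% use. The Cox results also depend on the ever-received reading.

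A reader might infer that the trial's treatment conclusion is at risk. It is not: the primary tests are log-rank tests without this factor, and the treatment HR and simulated region interaction barely move. The harm is confined to one exploratory covariate.

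**What to change.** In Poolability and Other Analyses, state that biologic receipt will be a time-dependent covariate in the Cox models (0 before the first dose, 1 after), counting only agents started with second-line chemotherapy before first progression of any kind. State also that it will not enter the P<.075 selection or the logistic models, and that the biologic intended at screening, if recorded, will be the baseline factor in those models.

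The line restriction is needed: for overall survival a time-dependent term that counts later lines gives an HR of 1.04-1.36 with no true effect, against 0.99-1.01 when restricted to second line.

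The cost is one covariate definition and slightly more analysis work, using dates of first dose; these should be available because Table 1 has concurrent medication recorded throughout. Three downsides remain. Confounding by indication is not removed: if 10% of still unseen progressions also block the start (assumed), the time-dependent PFS HR is 0.96-0.99. Intended use answers a somewhat different question from receipt. And the article says the intended biologic is decided, not that it is recorded; if it was not, the response and disease control models carry no biologic factor. Treatment rules, sample size and primary tests are unchanged.

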## Results

After the first 20 patients in the TARE group received TheraSphere microspheres followed by at least two cycles of chemotherapy, a feasibility safety assessment was conducted. The IDMC reviewed the safety results of both groups in an unblinded fashion. A consideration for adjusting the dose of cytotoxic agents, other safety recommendations, or stopping further enrollment could have been made if there was either an unanticipated patient death definitely or probably related to the sequential administration of TARE with oxaliplatin-based or irinotecan-based chemotherapy or there was a pattern of serious toxicity clearly related to the sequential administration of TARE with oxaliplatin-based or irinotecan-based chemotherapy. However, the IDMC did not recommend any changes to the study.

Enrollment for the study completed in October 2018. Results of the first interim analysis were reviewed by the IDMC, and their recommendation was to continue the study without any changes.

## Discussion

### Overview

First-line chemotherapy regimens for unresectable mCRC are well established [10]. Second-line therapy using the combination of chemotherapy and targeted therapies has demonstrated efﬁcacy with improved overall survival, progression-free survival, and overall response rate in comparison with chemotherapy alone [26,27]. However, the choice of the optimal treatment strategy remains challenging and is mostly driven by the type of and response to the first-line treatment administered, the type of retrovirus-associated DNA sequence mutation (KRAS, NRAS, and HRAS), microsatellite stability, tumor burden, patient performance status, and comorbidities.

The EPOCH study was designed to account for known prognostic and predictive factors [10]. Patients in the EPOCH study are stratified at randomization according to key factors that could influence the primary or secondary study end points: (1) tumor load (unilobar vs bilobar), (2) KRAS status (wild type vs mutant), and (3) prior first-line chemotherapy (oxaliplatin-based or irinotecan-based) to ensure balance between groups.

High tumor load is a known factor of chemotherapy failure [28]. KRAS mutation is a predictive factor of nonresponse to epidermal growth factor receptor inhibitor treatment [29,30]. Whether KRAS mutation is a prognostic factor is widely debated. KRAS mutant patients may have different sensitivity to treatment compared with KRAS wild-type patients [31-35], and KRAS mutational status will drive the postprogression treatment received. Second-line treatment with irinotecan-based regimens has been associated with shorter median progression-free survival [36]. Tumor sidedness is currently undergoing intense study, given the recognition that tumor location is prognostic and predictive [37-39]. Tumor sidedness is not a stratification factor in the EPOCH study because when the study was designed, the importance of this prognostic factor was less understood; however, a preplanned analysis to assess the impact of this factor will be performed. In addition, the impact of important covariates, such as asynchronous or metachronous metastases, location of primary tumors (right vs left), presence of lung or lymph node lesions at baseline, and biological agents received, will be assessed. This study was designed before well-established data on the prognostic significance of BRAF mutations were available, and thus, BRAF mutation status was not collected on the electronic case report forms. However, because BRAF mutant tumors are often right sided, the preplanned analysis to assess the impact of right-sided vs left-sided primary tumor location should provide an indirect assessment of BRAF mutation status.

TARE treatment for patients with liver or liver-dominant disease has been outlined in prospective and retrospective studies that have demonstrated that this option was manageable in this patient population and compared favorably with standard-of-care treatment [14-16,40,41]. The relevancy of TARE in the first-line setting was extensively explored in the pooled analyses of the randomized studies FOXFIRE, SIRFLOX, and FOXFIRE-Global [42,43]. This analysis demonstrated that TARE (with ^90^Y resin microspheres) in association with an oxaliplatin- and fluorouracil-based chemotherapy regimen failed to improve overall survival and progression-free survival compared with chemotherapy alone. However, the combination of TARE with first-line oxaliplatin-based chemotherapy significantly improved response rate and liver-specific progression-free survival in comparison with chemotherapy alone. In spite of an increased toxicity in the TARE group, the quality of life was not significantly different between the 2 treatment groups [42-44]*.* Factors that may have contributed to the failure of the previous ^90^Y resin microspheres trials are a long delay between randomization to starting TARE treatment, the percentage of patients with extrahepatic metastatic disease at baseline (40% of patients enrolled), the lower percentage of patients in the TARE group who received postprogression therapies, and inferior chemotherapy dose intensity in the TARE group.

In the EPOCH study, the patient population and treatment schedule were selected to avoid these factors that may have contributed to the failure of the previous first-line trials. Patients with rapid and diffuse progression of disease and those with extrahepatic metastasis are not eligible to participate, thus limiting the risk of the trial not reaching a primary progression-free survival end point because of extrahepatic progression. In addition, to avoid a discrepancy between the 2 treatment groups regarding chemotherapy intensity and the delay to start the attributed treatment, the 2 groups must start the first study treatment, that is, chemotherapy, within 21 days after randomization. Both groups also receive an optimal dose of chemotherapy based on oncologist determination. No dose reduction was preplanned in the TARE group. The safety of the treatment schedule was evaluated after the treatment of 20 patients, and the schedule was considered safe by the IDMC. Limitations of the study include the unblinded design, which is required for such a complex treatment intervention when it would be unethical to consider a *sham* procedure for the control group.

### Conclusion

It is important to establish an effective and tolerable treatment to improve patient outcome for unresectable liver metastases from colorectal cancer. One challenge in the treatment of mCRC patients with liver-dominant disease is providing an efficient treatment of the cancer without impairing liver function and allowing systemic treatment to continue with minimal interruption. TARE has a limited toxicity profile when used appropriately and, consequently, a low impact on the dose intensity and duration of systemic treatment. Enrollment for the EPOCH study completed in October 2018. Data from this trial will enhance the knowledge base regarding optimal treatment options for patients with unresectable mCRC.

## Appendix

Multimedia Appendix 1 IRB approval letter for the principal investigator of the multicenter study.

## Abbreviations

^90^Y: yttrium-90
^99m^Tc-MAA: technetium-99m macroaggregated albumin
CT: computerized tomography
ECOG: Eastern Cooperative Oncology Group
EPOCH: A Phase 3 Clinical Trial Evaluating TheraSphere in Patients with Metastatic Colorectal Carcinoma of the Liver who have Failed First Line Chemotherapy
FACT-C: Functional Assessment of Cancer Therapy-Colorectal Cancer
HR: hazard ratio
IDMC: independent data monitoring committee
KRAS: Kirsten retrovirus–associated DNA sequence
mCRC: metastatic colorectal cancer
MRI: magnetic resonance imaging
RECIST: Response Evaluation Criteria in Solid Tumors
SPECT: single-photon emission computed tomography
TACE: transarterial chemoembolization
TARE: transarterial radioembolization
